### Participants

2.3

A total of 90 patients undergoing secondary prevention for CVD will be recruited from a health center in Alicante, Spain. The target population will consist of patients undergoing secondary prevention for CVD who are receiving treatment with statins, (ACE) inhibitors/ (ARBs) at a single daily dose, and acetylsalicylic acid (ASA). The inclusion criteria are: (1) adults of both sexes, aged 18 years or older, who provide written informed consent after reading the patient information sheet; (2) patients receiving daily single-dose (ACE) inhibitors/ (ARBs), ASA, and statins for at least 6 months as part of secondary prevention; (3) diagnosis of cerebrovascular disease, ischemic heart disease or peripheral vascular disease; (4) patients under regular follow-up at our health center; and (5) patients identified with suboptimal therapeutic adherence, defined by the Haynes-Sackett test supplemented with a Medication Possession Ratio (MPR) < 80% for any of the three drugs in the past 6 months. The exclusion criteria include: (1) refusal to participate; (2) incomplete consent form; (3) language barriers; (4) psychiatric, psychological, neurological, or social conditions that impair the ability to participate in the intervention or follow-up; (5) life expectancy of less than 1 year; (6) patients whose drug management is handled by a caregiver (professional or family member); (7) Barthel Index score < 60; (8) institutionalized patients; and (9) patients currently enrolled in similar research studies.

Patients from our health center will be contacted by telephone, selecting those patients recorded in the electronic medical records with a coded diagnosis according to the International Classification of Diseases, Tenth Revision (ICD-10) of cerebrovascular disease, ischemic heart disease, and peripheral vascular disease in secondary prevention for CVD, who are prescribed all three drugs and meet the inclusion criteria while not presenting any exclusion criteria outlined in the study protocol. They will be informed about the study, and those who confirm their participation will be scheduled for an in-person appointment (with a companion, if possible, to also involve them in the intervention).

During the first consultation with the principal investigator, patients will be invited to participate in the study, proceeding to verify compliance with the selection criteria. To evaluate TA, the Haynes-Sackett test will be administered, supplemented by the MPR from the medical history, reviewing the year prior to the consultation. The purpose of the research will be explained, along with informed consent and its signing. Additionally, a patient information sheet will be provided.

### Intervention group

2.4

The intervention will consist of health education based on the recommendations of the CCM, with the aim of empowering patients for effective disease management through therapeutic education and shared decision-making. Two individual sessions will be conducted (one in the first month and another in the fourth month) and four group sessions (one each quarter, with participant numbers ranging from 5 to 10). Individual sessions will last 30 min, while group sessions will last 1 h.

In the first trimester, one individual session will be held (in the first month), followed by a group session (in the second month). In the second trimester, an additional individual session will take place (in the fourth month), along with a group session (in the sixth month), followed by subsequent group sessions scheduled for the ninth and twelfth months. These sessions will address the following components:Health education: emphasize the significance of TA and the objectives to be achieved, providing patients with information on the consequences of inadequate treatment adherence. Enhance patients’ understanding of their condition, potential adverse effects of drugs, how these may affect their well-being, and strategies for managing these effects. Clarify the benefits of adherence while exploring personal beliefs, concerns, and resistance to treatments, taking into account the patient’s cultural background. Highlight the importance of controlling additional CVRF, such as blood pressure, blood glucose, and weight, along with recommendations regarding the advantages of adhering to a Mediterranean diet.Mobile phone utilization: encourage the use of mobile phones as reminders for drug adherence through alarms and the ti.care® application.Drug verification: confirm that the drugs and dosages taken by the patient align with the prescribed regimen.MCAs: implement this system in collaboration with the patient’s community pharmacy at no cost.Shared responsibility: inform patients about the concept of shared responsibility and the importance of collaborative decision-making to achieve optimal health outcomes.Drug interchangeability: educate patients that their community pharmacist should not make substitutions between drugs bioequivalence with differing appearances.Empathetic approach: foster an empathetic atmosphere that avoids blame, promoting active listening and understanding.Empowerment: equip patients with the necessary skills to manage their own conditions, thereby fostering autonomy.

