### Study design

2.2

Open label randomized controlled trial, selecting patients presenting the inclusion criteria through consecutive non-probability sampling. The participants will be randomly assigned to either the intervention or control groups using a random number table. An intervention will be conducted on a group of patients (intervention group), and its outcomes will be compared to those of the control group, which will receive standard follow-up under routine clinical practice conditions. The follow-up will last for 1 year, at the conclusion of which the primary and secondary variables will be assessed. Nevertheless, an evaluation will be conducted at 6 months, and if significant benefits are evident, the study will be terminated.

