### Statistical analysis

2.7

The data will be analyzed using version 23.0 of the Statistical Package for the Social Sciences (SPSS), developed by IBM Corp. (Armonk, NY) for Windows, and the analysis will be performed with masking of third parties.

First, a univariate descriptive analysis will be conducted for qualitative variables, expressed as percentages, and for quantitative variables, expressed as means and standard deviations, with 95% confidence intervals calculated in all cases. Additionally, a bivariate analysis will be performed to identify associations between the intervention and changes in the parameters outlined in the study objectives, with particular focus on TA. Finally, a multivariate analysis will be carried out to isolate potential confounding factors and assess the impact of the intervention on TA, adjusted for the remaining studied variables. Statistical significance will be established with a *p*-value of less than 0.05.

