### Sample size calculation

2.8

Based on a TA rate of 50% in the control group and 80% in the intervention group, with a type I error of 5% (95% confidence interval), a type II error of 20% (80% power), and accounting for a 15% loss to follow-up, the final sample size will be of 45 patients per group.

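### Group delivery in the intervention arm only is not allowed for in the sample size or the described analysis; if outcomes correlate within session groups, power falls below 80% and type I error exceeds 5%

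*Protocol article*

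**What the plan says.** Randomisation is by patient (Protocol article, 2.2 Study design): "The participants will be randomly assigned to either the intervention or control groups using a random number table".

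The intervention arm is offered six sessions (2.4 Intervention group): two individual ones of 30 minutes and "four group sessions (one each quarter, with participant numbers ranging from 5 to 10", each lasting one hour. Group time is therefore 4 × 1 h = 4 of 5 contact hours. Section 2.5 describes routine family-physician consultations for controls and no group sessions.

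The sample size section (2.8) concludes that "the final sample size will be of 45 patients per group". It gets there from five inputs: adherence of 50% among controls, adherence of 80% with the intervention, α of 5%, power of 80% and attrition of 15%. It mentions no intra-cluster correlation, design effect or number of groups.

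The analysis (2.7) says "a bivariate analysis will be performed to identify associations between the intervention and changes in the parameters" named in the objectives, followed by a multivariate analysis adjusted for the other study variables. Section 2.6.1 lists those variables, and session group is not one of them.

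**The concern.** Patients are randomised one by one, but most of the intervention reaches them in small groups. Section 2.4 has the sessions explore beliefs, concerns and resistance to treatment, which may depend on who else is in the room. If so, adherence within a group will be correlated. Controls have no such grouping, so the design would be partially nested: clusters in one arm, singletons in the other.

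If that correlation is positive, the variance of the intervention-arm adherence rate is larger than the binomial variance for independent patients. A test that ignores this rejects too often, and a sample size that ignores it is too small for a test that does not. Ignoring the grouping in the test favours declaring the intervention effective.

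**Working it through.** **Inputs.** From 2.8: p₁ = 0.50, p₂ = 0.80, α = 5% (taken as two-sided, from the mention of a 95% confidence interval), power 80%, loss 15%, 45 per arm. From 2.4: 5 to 10 patients per group session. The ICC is not in the document; 0.01 to 0.10 is assumed.

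**1. Reproduce the stated sample size, assuming independent patients.** With pooled p̄ = 0.65:

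n = [1.96·√(2·0.65·0.35) + 0.8416·√(0.25 + 0.16)]² / 0.30² = (1.322 + 0.539)² / 0.09 = 38.5, so 39 evaluable per arm.

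Allowing for loss, 39 × 1.15 = 44.9 → 45, or 39/0.85 = 45.9 → 46. The arcsine formula gives 38, and 38/0.85 = 44.7 → 45. The stated 45 is therefore an independent-patients figure.

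**2. Reserve.** 45 × 0.85 = 38.25, so about 38 evaluable per arm. Power = Φ[(0.30 − 1.96·0.1094)/0.1039] = Φ(0.823) = 79.5%. Nothing is left to absorb clustering.

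**3. Number of groups.** 45/10 = 4.5 → at least 5; 45/5 = 9. Hence about 5 to 9 groups if each patient stays in one.

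**4. Power with the correct variance.** The design effect DE = 1 + (m − 1)·ICC multiplies the intervention-arm variance only, with m the group size:

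SE₀ = √[0.65·0.35·(1 + DE)/38], SE₁ = √[(0.25 + 0.16·DE)/38], power = Φ[(0.30 − 1.96·SE₀)/SE₁].

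Example, m = 10 and ICC 0.05: DE = 1.45, SE₀ = 0.1211, SE₁ = 0.1126, power = Φ(0.556) = 71.1%.

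**5. Type I error if grouping is ignored.** With equal true rates, α* = 2·{1 − Φ[1.96·√(2/(1 + DE))]}. Here the 38 evaluable patients are split into 5 to 9 groups, so m = 38/5 = 7.6 down to 38/9 = 4.2. Example, 5 groups and ICC 0.05: DE = 1 + 6.6·0.05 = 1.33, α* = 6.9%. A beta-binomial simulation at 50% versus 50% with the uncorrected two-proportion test agrees closely; repeat runs differ by up to about 0.2 points, and at ICC 0 the test itself gives 5.1%.

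| Assumed ICC | Power, 5 to 10 per group | Enrolled per arm for 80% power | Type I error, 9 to 5 groups (formula) | Same, simulated |
|---|---|---|---|---|
| 0 | 79.5% | 46 | 5.0% | 5.1% |
| 0.01 | 78.7% to 77.8% | 48 to 49 | 5.2% to 5.4% | 5.2% to 5.4% |
| 0.02 | 78.0% to 76.1% | 48 to 50 | 5.4% to 5.8% | 5.5% to 5.9% |
| 0.05 | 75.7% to 71.1% | 51 to 56 | 5.9% to 6.9% | 6.0% to 7.1% |
| 0.10 | 72.0% to 63.5% | 55 to 65 | 6.9% to 8.9% | 7.0% to 9.0% |

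The power column spans the planned group sizes, so its lower end assumes ten evaluable patients in every group. At m = 7.5, close to the five-group case after losses, power is 78.2%, 77.0%, 73.4% and 67.6% at the four positive ICCs. All power figures use a normal approximation; small-sample degrees of freedom with 5 to 9 groups would lower them further.

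**The case against.** A reader might infer that the standard errors are certainly too small and the 80% power certainly overstated. The document does not support that. Both need a positive within-group correlation and reasonably stable groups, and it gives neither. It does not say that the same patients meet in all four group sessions; if groups are re-formed each quarter, the correlation is diluted and simple nesting does not apply. It does not say how many people lead the sessions, so a facilitator effect is conjecture. Several components act on the individual (drug verification, compliance aids through the patient's own pharmacy, phone reminders), and two sessions are one-to-one. The last group session falls in month 12, when the outcome is due, so it can hardly shape the preceding year's refills. All this favours the low end of the assumed range, where the loss is about 1 to 3 points of power. These arguments stand, and they limit the size of the point.

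A reader might also reach a type I error of about 10% by assuming four groups at ICC 0.10. With at most 10 per group, 45 patients need at least five, and the figure is then about 9%.

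Finally, 2.7 is a condensed summary that names no test or model, and a fuller analysis plan may deal with correlation. That stands as far as the model is concerned, so the analysis part is weaker than the sample-size part. It does not rescue 2.8, which states all its inputs and reproduces only with independent patients, nor does it add session group to the variables in 2.6.1.

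**Conclusion.** The point holds in conditional form. The mismatch is established from the text: group delivery in one arm, an independent-patients sample size with no reserve, and no session-group variable among those listed. Its consequence depends on an ICC that the document does not give. It is minor at 0.01 to 0.02. At 0.05 power drops by about 4 to 8 points from 79.5%, and at 0.10 by about 7 to 16 points, with type I error reaching roughly 7% and 9% respectively when there are five groups. The direction is the same for any positive correlation. The point deserves action because session membership is hard to reconstruct if it is not recorded during delivery.

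**What to change.** - In 2.4, state whether session groups are fixed or re-formed. In 2.6.1, add the session group attended by each intervention patient at every group session.
- In 2.7, specify for the primary endpoint an analysis that allows for clustering in the intervention arm only, with controls as singletons and a small-sample correction, at least as a pre-specified sensitivity analysis. A random-intercept model as the sole primary analysis is debatable: 5 to 9 groups estimate a variance component poorly. Nor does this point require groups to be held fixed; recording membership is enough.
- In 2.8, restate the power at 45 enrolled per arm (about 38 evaluable) over an assumed ICC range such as 0.01 to 0.10, with the group size used.

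The cost is one extra recorded variable, slightly wider intervals and a less favourable stated power. Recruitment need not change unless the sponsor wants to keep 80% power at a given ICC, in which case the enrolment figures above apply.

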### Control group

2.5

In the control group, patients will receive follow-up care under standard clinical practice conditions, which typically involve routine consultations with their family physician. During these visits, the emphasis is primarily on monitoring CVRF and assessing drug adherence based on the information shared by the patients. While this conventional approach provides essential support, it may not always encompass structured educational interventions or personalized strategies to increase TA.

### Study variables

2.6

The main variable to evaluted will be TA using the Haynes-Sackett test to determine adherence vs. non-adherence (a dichotomous qualitative variable), complemented by the MPR to calculate a percentage (a continuous quantitative variable). Good TA is defined as responding that the patient experiences no difficulties taking all prescribed tablets and has an MPR > 80% for the three preventive drugs. Conversely, if these conditions are not met, it is classified as poor TA. Poor TA, based on the MPR, is indicated if the patient has not picked up 20% or more of the prescribed packages from the pharmacy in recent years. A diagnosis of poor TA can be made using either method. Since three TA are analyzed, poor TA is established if it occurs with any one of them, two, or all three.

#### Secondary variables

2.6.1

Group: a binary qualitative variable (intervention or control group).Age: a continuous quantitative variable measured in years.Sex: a dichotomous qualitative variable (male/female).Race: a nominal qualitative variable.Level of education: an ordinal qualitative variable.Illiterate.Elementary school studies.Technical studies.Secondary Education Studies.University studies.Degree of functional dependence in activities of daily living: a discrete quantitative variable measured using the Barthel Index.Quality of life: a categorical variable assessed using the EuroQol- 5 Dimension (EQ-5D). It consists of two parts: in the first, the patient evaluates their health status, and the second part utilizes a visual analog scale (VAS) from 0 to 100.

### Statistical analysis

2.7

The data will be analyzed using version 23.0 of the Statistical Package for the Social Sciences (SPSS), developed by IBM Corp. (Armonk, NY) for Windows, and the analysis will be performed with masking of third parties.

First, a univariate descriptive analysis will be conducted for qualitative variables, expressed as percentages, and for quantitative variables, expressed as means and standard deviations, with 95% confidence intervals calculated in all cases. Additionally, a bivariate analysis will be performed to identify associations between the intervention and changes in the parameters outlined in the study objectives, with particular focus on TA. Finally, a multivariate analysis will be carried out to isolate potential confounding factors and assess the impact of the intervention on TA, adjusted for the remaining studied variables. Statistical significance will be established with a *p*-value of less than 0.05.

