### Aims and objectives

2.1

The primary aim of this study is to evaluate the efficacy of an intervention through health education based on the Chronic Care Model’s implementation to increase TA in patients with secondary prevention for CVD.

Other secondary objectives are:Evaluate the efficacy of an intervention based on the implementation of the CCM on the control of cardiovascular risk factors (CVRF).Assess whether the intervention affects the improvement of patients’ quality of life.Determine TA in patients undergoing secondary prevention for CVD.Compare differences in TA based on sex, age, race, and education level.Identify modifiable factors associated with poor TA.

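### Quality of life is compared between arms only as an unadjusted change; for the EQ-5D VAS, adjusting for the baseline score would generally be more precise at almost no cost

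*Protocol article*

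**What the plan says.** Section 2.1 (Aims and objectives) lists as a secondary objective: "Assess whether the intervention affects the improvement of patients’ quality of life". That is a question about a difference between arms.

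Section 2.6.1 (Secondary variables) measures quality of life with the EQ-5D. It labels the variable categorical and describes two parts, of which "the second part utilizes a visual analog scale (VAS) from 0 to 100".

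Section 2.7 (Statistical analysis) has three steps: a descriptive summary; a bivariate step, in which "a bivariate analysis will be performed to identify associations between the intervention and changes in the parameters outlined in the study objectives"; and a multivariate step meant to "assess the impact of the intervention on TA, adjusted for the remaining studied variables". The significance rule is the same throughout: "Statistical significance will be established with a *p*-value of less than 0.05".

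The bivariate step covers every objective, including quality of life. The multivariate step names TA alone as its outcome. No stated model uses a baseline EQ-5D value.

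**The concern.** A change from entry to month 12 cannot be calculated without the entry score. If changes are analysed, the baseline value is therefore available, but the stated analysis uses it only by subtraction. In a randomised comparison of a continuous score, subtraction is usually not the most efficient use of baseline, for two reasons.

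- **Precision.** The change score carries the measurement noise of both occasions. Regression on baseline removes only the part of the month-12 variation that baseline predicts.
- **Chance imbalance.** Subtraction removes the whole baseline difference between arms, although only a fraction of it is expected to persist to month 12. The arm that happens to start lower then appears to improve more, through regression to the mean.

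Section 2.8 sizes the trial on binary adherence only, so no power has been planned for quality of life and there is none to spare. A real difference on the VAS is more likely to be missed than the collected data require, and with some 40 patients per arm the estimate can be moved noticeably by the starting difference.

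**Working it through.** **1. The plan's own sample size.** Section 2.8 starts "Based on a TA rate of 50% in the control group and 80% in the intervention group", with 5% type I error, 80% power and 15% loss. The usual two-proportion formula (pooled, two-sided, no continuity correction) gives:

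n = [1.960·√(2·0.65·0.35) + 0.842·√(0.5·0.5 + 0.8·0.2)]² / 0.30² = 38.5, so 39 per arm.

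Allowing for loss gives 39 × 1.15 = 45 or 39 / 0.85 = 46. The stated 45 per group reproduces and is not affected by this point. The article gives no corresponding figure for EQ-5D.

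**2. Inputs for the VAS comparison.**
- From the article: 45 per arm, 15% loss, significance level 0.05. Evaluable patients: 45 × 0.85 = 38.25, taken as 38 per arm.
- Assumed, because the article does not give them: a two-sided test; baseline to month-12 correlation rho (range shown); equal SDs at baseline and month 12, set to 1; a true effect of 0.5 SD; a linear model for the VAS.

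**3. Variance per patient.**
- Change score: 2(1 − rho)
- Month-12 score adjusted for baseline (ANCOVA): 1 − rho²
- Ratio, ANCOVA to change: (1 + rho)/2, which is below 1 whenever rho is below 1

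**4. Power.** Noncentral t, 74 degrees of freedom, noncentrality 0.5 / √(2·variance/38):

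| rho | Variance, change | Variance, ANCOVA | Ratio | Power, change | Power, ANCOVA | Gain (points) |
|---|---|---|---|---|---|---|
| 0.3 | 1.40 | 0.91 | 0.65 | 44.4% | 61.6% | 17 |
| 0.5 | 1.00 | 0.75 | 0.75 | 57.6% | 70.0% | 12 |
| 0.7 | 0.60 | 0.51 | 0.85 | 79.3% | 85.4% | 6 |
| 0.8 | 0.40 | 0.36 | 0.90 | 92.5% | 94.8% | 2 |

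Using 73 degrees of freedom for ANCOVA leaves these figures unchanged to the first decimal or within 0.1 point. For a 0.65 SD effect at rho 0.5, power is 79.9% for change and 89.8% for ANCOVA.

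**5. Chance imbalance.** The baseline difference between arms has standard error √(2/38) = 0.229 SD. The change score removes all of it where only rho times it should be removed, so (1 − rho) times the imbalance enters the estimate. At rho 0.5, an imbalance of one standard error shifts the estimate by 0.5 × 0.229 = 0.11 SD, in favour of the arm that started lower.

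**6. Sensitivity to the equal-SD assumption.** With baseline SD s0 and month-12 SD s1, the variance saved by ANCOVA is (s0 − rho·s1)². It is never negative, but it is zero when s1 = s0/rho. Example with rho 0.7, s0 = 1 and s1 = 1.25:
- Change: 1 + 1.5625 − 2·0.7·1.25 = 0.8125
- ANCOVA: 1.5625 × 0.51 = 0.7969
- Saving: 0.0156 / 0.8125, about 2%, against 15% with equal SDs

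**The case against.** **The method is only loosely described.** Section 2.7 is a short summary in a condensed article. It names no test, and the word for changes could be loose wording for effects. The exact model for a secondary patient-reported outcome is often left to a statistical analysis plan, and nothing in the section forbids an adjusted EQ-5D analysis. This lowers the weight of the point but does not remove it. The section does choose a quantity (changes) and a method (bivariate), and it names an adjusted model for TA only. The objective itself speaks of improvement, which supports reading the quantity as change from entry.

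**The outcome is labelled categorical.** This stands as a limit. The formulas and the proposed model apply to the 0 to 100 VAS and not to a categorical EQ-5D profile.

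**A baseline EQ-5D is not explicitly scheduled.** This also stands. Section 2.3 names only the Haynes-Sackett test and the medication possession ratio at the first visit, and section 2.2 places assessment of the secondary variables at the end of follow-up. A baseline EQ-5D is implied by the analysis of changes, not stated.

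**The size is assumed.** Correlation, SDs and effect size are not in the article, and the gain is small if rho is about 0.8 or if the month-12 SD is moderately larger than the baseline SD.

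Three stronger readings are tempting and not supported:
- A reader might infer that adherence receives a baseline adjustment that quality of life is denied. The TA model is described as adjusted for the other studied variables, and a baseline TA value is not named. Because entry requires suboptimal adherence, baseline TA status would hardly vary in any case.
- A reader might infer that the planned comparison is biased or inflates false positives. Under randomisation it does neither on average; the shift exists only given the imbalance that occurs.
- A reader might infer that adjustment is substantially better for every rho below 1. That depends on the equal-SD assumption, as step 6 of the working shows.

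**Conclusion.** The point holds as an efficiency matter for one secondary objective. As written, section 2.7 gives quality of life an unadjusted comparison of change, which for the EQ-5D VAS is valid but generally less precise than adjusting for baseline and over-corrects a chance imbalance. Under the stated assumptions the power forgone for a 0.5 SD effect runs from about 17 points at rho 0.3 to about 2 points at rho 0.8, and it shrinks further if the month-12 SD moderately exceeds the baseline SD. The primary adherence analysis and the sample size are untouched. The change is worth making because it is nearly free, but leaving it would not invalidate the trial.

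**What to change.** In section 2.7, state that the EQ-5D VAS at month 12 will be analysed with a linear model containing arm and baseline VAS, and that the adjusted mean difference will be reported with its 95% CI. Keep the unadjusted change in each arm as a descriptive summary. Because section 2.6.1 calls quality of life categorical, say there that this analysis concerns the VAS part. Confirm that the EQ-5D is recorded at entry.

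Cost: a sentence or two of text and one degree of freedom, in a model that SPSS fits directly. No extra patients are needed. No new data are needed either, provided the entry EQ-5D is collected as an analysis of changes already implies. The sentence should be fixed before outcome data are seen by arm, so that no choice between adjusted and unadjusted results remains open.

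### Adjusting the adherence effect for every other studied variable overloads the model and leaves the one-year EQ-5D value open as a covariate

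*Protocol article*

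**What the plan says.** Section 2.7 (Statistical analysis) plans descriptive statistics, then a bivariate analysis with emphasis on therapeutic adherence (TA), then a multivariate analysis. The last is meant to deal with confounding and to "assess the impact of the intervention on TA, adjusted for the remaining studied variables". It does not shorten the list, limit it to baseline values or give a selection rule.

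Section 2.6.1 (Secondary variables) supplies the list: group, age, sex, race (nominal), education (ordinal, five levels), Barthel Index, and quality of life, introduced as "Quality of life: a categorical variable assessed using the EuroQol- 5 Dimension (EQ-5D" and including a 0–100 visual analogue scale (VAS).

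Quality of life is also an outcome. A secondary objective in section 2.1 is to "Assess whether the intervention affects the improvement of patients’ quality of life". Section 2.2 (Study design) places assessment of the primary and secondary variables at the end of the one-year follow-up.

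Section 2.8 (Sample size calculation) assumes a "TA rate of 50% in the control group and 80% in the intervention group" and, "accounting for a 15% loss to follow-up", concludes that "the final sample size will be of 45 patients per group".

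**The concern.** Two things follow from the adjustment sentence as written.

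- **Too many terms.** With a binary outcome, the rarer category limits how many coefficients can be estimated. A trial of 90 patients cannot carry the whole list. In a logistic model with few events per coefficient, the treatment odds ratio drifts away from 1 and becomes less precise. The published effect would then look larger than it is.
- **An outcome may become a covariate.** EQ-5D is in the list and is measured after randomisation. Conditioning on its follow-up value can open a non-causal path between group and adherence, which randomisation does not protect against.

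The two faults push the estimate in opposite directions, so a reader could not tell which had prevailed.

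**Working it through.** **Sample size, reproduced.** Inputs from section 2.8: 50% v 80%, type I error 5% (two-sided assumed), power 80%, loss 15%. Pooled two-proportion formula without continuity correction:

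n = [1.96·√(2·0.65·0.35) + 0.8416·√(0.5·0.5 + 0.8·0.2)]² / 0.30² = (1.322 + 0.539)² / 0.09 = 38.5, so 39 per group.

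39 × 1.15 = 44.9, so 45, as stated (39 / 0.85 gives 46, a trivial difference). The trial was therefore sized on a simple unadjusted comparison. After 15% loss, 45 × 0.85 = 38 per arm.

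**Patients in the rarer category.** Non-adherent = 38 × (0.5 + 0.2) = 26.6. With no loss at all, 45 × 0.7 = 31.5.

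**Non-adherent patients per term, at 38 per arm**

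| Coding (including group) | Terms | Per term |
|---|---|---|
| Age, sex, two-level race, education as one score, Barthel, VAS | 7 | 26.6/7 = 3.8 |
| As above plus an EQ-5D summary score | 8 | 26.6/8 = 3.3 |
| The 7-term set with education as 4 dummies | 10 | 26.6/10 = 2.7 |
| The 8-term set with education as 4 dummies and three-level race | 12 | 26.6/12 = 2.2 |

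With no loss, 7 and 8 terms give 4.5 and 3.9. By the common convention of about 10 per term, the data support 26.6/10 = 2.7 terms; at 5 per term, 5.3. Even the most favourable split of 76 patients (38 adherent, 38 not) gives only 38/8 = 4.8 per term.

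**Effect on the estimate.** True odds ratio = (0.8/0.2)/(0.5/0.5) = 4. Logistic models were simulated at 38 per arm with covariates unrelated to outcome, so the adjusted and unadjusted true values coincide and any shift is small-sample bias. Runs with separation are left out of the medians.

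| Terms | Median OR | SD of log OR |
|---|---|---|
| Group only | 4.0–4.2 | 0.56 |
| 7 | about 4.7 | – |
| 8 | about 4.9 | 0.70 |
| 10 | about 5.2 | – |
| 12 | about 5.5 | 0.78 |

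Rejection under the null was 5.4% with group only, 7.0% with 8 terms and 6.8% with 12 (2,000 runs each, simulation error about ±1 point). A separate check gave about 6%. Power hardly moved: 0.79 unadjusted, 0.78 with 8 terms, 0.77 with 12. The damage is mainly to the size and precision of the reported effect.

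**If the one-year quality-of-life score enters.** Suppose the score has unit SD, adherence shifts it by a, and the intervention shifts it directly by d. For a normal score, the adjusted log odds ratio is ln 4 − a·d. The values of a and d are assumptions; the documents give none.

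- a = 0.5, d = 0.3: 4·e^(−0.15) = 3.4 (simulated 3.46)
- a = 0.5, d = 0.5: 4·e^(−0.25) = 3.1 (simulated 3.12)
- a = 0.8, d = 0.5: 4·e^(−0.40) = 2.7 (simulated 2.67)
- d = 0: 4.0, no shift (simulated 3.95–3.97)

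Simulated power at 38 per arm in the first three cases was 0.65, 0.55 and 0.42, against about 0.79 unadjusted.

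**The case against.** **The EQ-5D bias is conditional.** A reader might infer that the plan certainly adjusts for the follow-up value. The text does not say so. The stated purpose is to handle confounders, which points to baseline characteristics. The end-of-study timing in section 2.2 cannot settle it either, because the variables headed secondary include group, age and sex. With a baseline value this bias disappears; with a follow-up value it also disappears if the intervention acts on quality of life only through adherence. This part of the objection stands: the fault is that the wording permits such an adjustment.

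**The model need not be very large.** A reader might infer at least 10 parameters, or 20 and more with the EQ-5D dimensions as categories, and frequent failure to fit. Education is called ordinal and can be one score, giving 7 or 8 terms. Separation was then about 2%. The rate of 24% seen with 12 terms depends on category frequencies that the documents do not give, and no passage says that the dimensions enter separately. This also stands, but it does not rescue the plan: the odds ratio is overstated under every coding tried.

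**Two further readings go too far.** Leaving the baseline Medication Possession Ratio (MPR) out of the covariate list is not an error, and any power gained by adjusting for it would rest on a correlation that the documents do not supply. Nor is the absence of a ranking between the bivariate and multivariate analyses a fault in itself, since an article may leave that to the full protocol or analysis plan. The bivariate comparison matches the sample size basis, so the overloaded model may not be the main test.

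The adjustment set is different: the article does fix it.

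**Conclusion.** The concern holds in a limited form. Followed as written, the adjusted adherence model has fewer than 4 non-adherent patients per term at 38 evaluable per arm, even with the leanest coding. It overstates a true odds ratio of 4 as about 4.7–4.9 (7–8 terms), 5.2 (10 terms) or 5.5 (12 terms), with type I error modestly raised to about 6–7%. This rests on the 50%/80% planning rates, 15% loss and a logistic model, which is inferred from the dichotomous outcome because no model is named.

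Bias through EQ-5D is possible but not established. It needs both the one-year value in the model and an effect of the intervention on quality of life outside adherence. The range of 2.7–3.5 illustrates its size under assumed effects and is not a prediction. The unadjusted comparison is untouched by either problem.

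**What to change.** In section 2.7, replace the instruction to adjust for all remaining studied variables with three statements:

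1. The adherence model contains group and one or two pre-specified baseline covariates, for example the lowest of the three drug-specific MPRs at screening, and age. State one look-back window for that MPR, because section 2.3 uses the past 6 months for eligibility and the prior year at the first consultation.
2. No variable measured after randomisation, including follow-up EQ-5D, is a covariate in that model.
3. One comparison is named in advance as primary. The unadjusted two-proportion comparison on which the trial was sized is acceptable, with the adjusted model supportive; the reverse is also acceptable if fixed before the data are seen.

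The cost is a change of wording, with no new data or patients. The downside is that the other listed variables are no longer adjusted for in the main adherence model and can appear only in exploratory analyses.
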